##### Missing data

Patient loss to follow-up is not uncommon in the primary care setting. Mitigation efforts include appointment reminders, follow-up by care navigators, and options for telemedicine visits. A 20% loss to follow-up has been factored into our sample size estimation. For covariates or confounders which are missing at 10% prevalence or less we will use multiple imputation (mice) [79] or related EM likelihood-based procedures for evaluations in Aim 3 [80].

##### Power considerations

We conducted power/sample size for this ROIO design trial to address primary aims, using developed formulas [81] drawn from stepped wedge designs that account for unequal cluster size and package *swCRTdesign* [82]. The design includes 4 identified clinics (clusters), at least one 3-month period in standard care and 4 additional periods where assigned clinics can transition to I-FRESH at 4-month intervals. We estimated the needed sample to test a 10% difference in proportions of engagement in services (i.e., Aim 2b healthcare and community program utilization), and a standardized mean increase of at least d ≥ 0.20 when reported at 6- and 12-month health outcomes. With alpha = 0.05, 4 clusters (1 clinic per cluster = 4 clinics with *n* = 300 - 500 potential patients in each clinic) and five periods of transitions (baseline and 4 clinics), we will maintain power > 0.83 to detect clinic differences (I-FRESH vs standard care) of >8% in rates of screening, referral and follow-up engagement in services and changes in acceptability ratings of d > 0.20 after implementing I-FRESH given a between clinic standard deviation of 0.05 in random treatment effects. Using an empirical approach, we simulated 1000 data sets with expected mean changes (d ≥ 0.20) and serial correlations similar to pilot samples. We used the percentage of growth models with *p* < 0.05 for slope parameters to estimate power given proposed sample of 60 per clinic and allowance for 20% missing data. With median slope of 0.02 (increase per month; estimate sd = 0.01) we observed significant effects in >81% of models suggesting sufficient power to detect desired effects in Aim 3 with the proposed sample.

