#### Specific Aim 2: Assess implementation outcomes

With each iteration of the roll-out, we will gather implementation outcomes from each level of the program: individual/family, hospital, and community partner level. Using the RE-AIM outcomes framework [32, 33], our primary implementation outcomes are feasibility and acceptability of I-FRESH by families, healthcare providers, ancillary support staff, administrators, community nutrition support programs, and community members. We will also assess fidelity, adoption, and reach of the program by assessing which components were carried out by ancillary health care staff/care navigator, staff/setting characteristics, and percentage of families who participated. Reach and maintenance of the program will be tracked through the EHR registry. (Further details on assessments are presented below in Measures.)

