Aim 1 Implementation Mapping and Optimization	• Adaptations and Implementation strategies • Barriers to program implementation • Structures and systems needed to implement program and support community programs • Experience with multi-component implementation • PRISM Fit assessment	H, Com H, Com H, Com P, H, Com P, H, Com	Periodic reflection, Interviews Periodic reflection, Interviews	Before, during, after each roll-out Before, during, after each roll-out
Aim 2 Implementation Outcomes	• Acceptability, Feasibility, Appropriateness of program [60] • Reach: % of families attending clinic that completed screener, # of families in the registry, % of families that did not want service, Characteristics of participating vs. non-participating families • Adoption: Characteristics of clinic settings and staff, Characteristics of community program (location, months/days/hours of operation, description of benefits or incentives, educational programs available) • Readiness for organizational change scale [61] • Implementation Climate Scale [62] • Implementation/Fidelity: % of families that were called, % of families that were referred or provided with resources, % of families that received follow-up phone calls, % of families that needed additional resources/referrals • Maintenance: • Program Sustainability Index [63] • Perceived support of innovation in organizations [64] • Partnership synergy tool [65–67]	P, H, Com H H, Com H H, Com	Periodic reflection, Interview, Survey EHR, Survey Survey, Periodic reflection EHR, Periodic reflection Survey	6, 12 mos Ongoing & 12 mos Ongoing & 12 mos Ongoing & 12 mos 12 mos

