#### Program acceptability, feasibility, and process evaluation

Quantitative and qualitative assessments of intervention acceptability and satisfaction will be collected from parents and providers/staff. For parents, we will administer self-report surveys (*n* = 60 per clinic) after they receive referrals and engage in nutrition support programs for 6- and 12-months. A random sample of parents (*n* = 10 per clinic, using a purposeful sampling method to include parents who successfully accessed programs and those who did not) will be invited to participate in a post-interview. The post-interviews will be conducted using a semi-structured interview guide probing relevant PRISM domains such as parents’ experience, usefulness, satisfaction, and recommendations for improvements with each program component, including concerns or barriers to accessing the CBOs, and interactions with health care providers, care navigators, and CBOs.

Providers, care navigators, and key health care administrators will also be invited to participate in a 45–60 minute group-based periodic reflection [34] (per active clinic) to determine challenges, opportunities, and modifications needed to optimize program implementation for the subsequent clinic roll-out. All participants will be invited to complete post-roll-out surveys (every 6 months) to assess impact, feasibility, acceptability, and appropriateness or fit of the program using the 4-item Acceptability of Intervention Measure (AIM), Intervention Appropriateness Measure (IAM), and Feasibility of Intervention Measure (FIM)) [60]. All interviews and periodic reflections will be audiotaped and transcribed verbatim for analysis.

At the community partner level, focus groups or key informant interviews will be conducted to determine the impact of referrals on their program (e.g., were they able to meet the increased demand) and what further improvements in communication are needed between the health care system and families. Final workflows and systems will be reviewed and refined by community stakeholders before being utilized in a fully-powered clinical trial.

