#### Quantitative data

Primary analyses for Aim 2 will assess fidelity and reach outcomes (Aim 2b) assessed within the EHR (e.g., screening, referrals, and follow-up assessments) and surveys (e.g., Acceptability, Feasibility, and Appropriateness) across the study period using Generalized Linear Mixed-effects Models (GLMM) and time-varying indices for clinics randomized to cross-over in each wave, time (secular trend), and clinic characteristics as planned covariates. Serial cross-sectional summaries for each clinic within monthly blocks will allow estimation of changes in clinic outcomes after crossing over into interventions. Primary analyses for Aim 3 will describe I-FRESH participants’ (*n* = 240) changes in health outcomes including: a) metabolic labs, BP, BMI, b) healthcare utilization; c) community program utilization; d) Quality of Life; e) Food Frequency Questionnaire and f) Knowledge, Skills, Attitudes, and Self-Efficacy. GLMM growth models for individual trajectories of continuous and limited categorical outcomes will include a focus on significance of changes from baseline to post-treatment assessments after graphically examining an appropriate functional form (e.g., linear or categorical) for modeling each outcome. All models will include participants’ characteristics (gender, ethnicity, parental education) and allocation clinic as planned covariates when estimating changes in primary health and engagement outcomes. We will explore the role of SDOH and implementation strategy effectiveness as potential influences in describing changes in parent and child health outcomes. Benjamini-Hochberg [78] procedures will be used to adjust *p*-values for inference decisions within common domains.

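### Acceptability ratings are collected only after roll-out, so the powered change against standard care cannot be estimated

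*Protocol article*

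**What the plan says.** Specific Aim 2 of the Protocol article states that "our primary implementation outcomes are feasibility and acceptability of I-FRESH".

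Three places give the timing of these ratings:

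- Table 1, Aim 2 row: the first entry is "Acceptability, Feasibility, Appropriateness of program", and the frequency column of that row begins "6, 12 mos Ongoing & 12 mos". Read in order, the ratings are taken at 6 and 12 months. Most Aim 3 entries in the same table start at month 0.
- Program acceptability, feasibility, and process evaluation, on parents (60 per clinic): they are surveyed "after they receive referrals and engage in nutrition support programs for 6- and 12-months".
- The same section, on the acceptability, appropriateness and feasibility scales: "All participants will be invited to complete post-roll-out surveys (every 6 months").

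Two places then use the ratings as if standard-care values existed. Quantitative data names these surveys, beside the EHR measures, in the mixed model with cross-over indicators and a secular trend, and says that monthly clinic summaries will show change after crossing over. Power considerations uses stepped-wedge formulas with 4 clinics, five periods and 300 to 500 potential patients per clinic. It claims power above 0.83 for I-FRESH against standard care, both for rate differences above 8% and for "changes in acceptability ratings of d > 0.20 after implementing I-FRESH".

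**The concern.** A stepped-wedge comparison takes its information from outcomes observed both before and after a clinic crosses over. If an outcome is measured only afterwards, there is no standard-care value to change from, and neither more patients nor a different model supplies one. The scales rate a programme, and the article does not say what would be rated before I-FRESH starts.

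Acceptability is one of the two outcomes named as primary for implementation, and it carries an explicit power figure. If the text stands, the analyst is told to fit a treatment effect that the data cannot identify, and readers are told that the trial is well powered for it. The number of raters is a second mismatch: the calculation cites clinic volumes in the hundreds, while the survey goes to 60 parents per clinic.

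**Working it through.** **Inputs from the Protocol article.** 4 clinics; one standard-care period and 4 transition periods; alpha 0.05; d = 0.20; SD 0.05 for the random treatment effect between clinics; 300 to 500 potential patients per clinic; 60 surveyed parents per clinic; 20% loss, which leaves 48 per clinic and 192 in all; up to 100 staff and advisory-board members in total.

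**Assumed because not stated.** Two-sided test; outcome SD 1; clinic SD 0 to 0.30; number of ratings per clinic-period, varied below; independent ratings in each clinic-period, in line with the serial cross-sectional summaries that the article describes.

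**Step 1: the plan's own figure.** Generalised least squares for the 4 × 5 stepped wedge, with fixed period effects, a random clinic intercept and a random treatment effect; power = Φ(0.20/SE − 1.96). Here only, control ratings are supposed to exist.

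| Ratings per clinic-period | Power, clinic SD 0 to 0.30 |
|---|---|
| 12 (60 spread over 5 periods) | 0.14–0.19 |
| 60 | 0.46–0.63 |
| 85 (60 parents + 100/4 staff and advisers) | 0.59–0.75 |
| 100 | 0.65–0.81 |
| 300 | 0.96–0.99 |
| 500 | 0.995–0.999 |

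The stated figure of above 0.83 cannot be confirmed or refuted exactly, because its inputs are incomplete. Under these assumptions it needs more than 100 ratings per clinic in every period, standard-care periods included.

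**Step 2: the documented schedule.** Remove every standard-care cell. Ten clinic-periods remain (4 + 3 + 2 + 1), all in periods 2 to 5. The model has 6 parameters: an intercept, 4 period effects and the treatment effect. The treatment indicator is 1 in every remaining cell and so cannot be separated from the intercept, and period 1 is not observed at all. The information matrix has rank 4 of 6. Without period effects it has rank 1 of 2. In neither case is the treatment effect estimable, whatever the sample size.

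**Step 3: what the schedule can estimate.**

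Change from 6 to 12 months under I-FRESH: SE = √(2(1 − ρ)/N), power = Φ(0.20/SE − 1.96).

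| Pairs | ρ = 0.3 | ρ = 0.5 | ρ = 0.7 |
|---|---|---|---|
| 240 | 0.75 | 0.87 | 0.98 |
| 192 | 0.65 | 0.79 | 0.95 |

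For example, with 192 pairs and ρ = 0.5, SE = √(1/192) = 0.072 and Φ(2.77 − 1.96) = 0.79.

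Mean rating at one time point, 95% half-width in SD units:

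- One clinic: 1.96/√48 = 0.28.
- Overall, ignoring clustering: 1.96/√192 = 0.14.
- Overall, clinic as a random effect with SD s: 1.96·√(s²/4 + 1/192), which is 0.15 at s = 0.05 and 0.33 at s = 0.30.

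**The case against.** The best defence is grammatical. In Power considerations the words about I-FRESH against standard care attach to the rate differences, and the acceptability clause could mean change over ratings taken after implementation. That quantity is estimable (step 3). But the clause shares one sentence and one power figure with a stepped-wedge calculation, and Quantitative data assigns the same surveys to the cross-over model. The reading therefore does not rescue the text as it stands; it shows what the text could be changed to say.

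It is also fair that the article's hypothesis is that the bundle is feasible and acceptable, which post-roll-out ratings can address without a control; that 300 to 500 describes clinic volume and suits the EHR rates; that staff and advisers also give ratings; and that the order of entries in Table 1 is read from a broken extraction. The last point matters little, because the measures text gives the same timing independently.

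Three stronger readings are tempting but not supported:

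- **That the survey is biased upward because only engaged families answer.** The wording "after they receive referrals and engage in nutrition support programs for 6- and 12-months" could be read so. But 60 per clinic is the whole Aim 3 enrolment target, recruited on a positive screen, and the interview sample deliberately includes parents who did not access programmes. The clause may only describe timing. Bias is a risk of the wording, not an established fact.
- **That there are two rival sets of primary outcomes.** Quantitative data says "Primary analyses for Aim 2 will assess fidelity and reach outcomes (Aim 2b) assessed within the EHR", but the same sentence goes on to name the acceptability and feasibility surveys.
- **That community program utilization has the same defect.** Power considerations labels it "i.e., Aim 2b healthcare and community program utilization" while Table 1 lists it under Aim 3. Read in order, Table 1 gives it a month-0 assessment, so it does not lack a baseline. The label is a cross-reference slip.

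**Conclusion.** The point holds for the ratings. Acceptability, feasibility and appropriateness have no scheduled standard-care observation, so their I-FRESH effect against standard care is not estimable, and the power figure above 0.83 does not apply to acceptability. The power sentence names acceptability alone; feasibility and appropriateness are affected through the shared schedule and model. This conclusion rests on the documented timing and on no assumed number.

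The sample-size mismatch is secondary and depends on assumptions. If control ratings existed, 60 per clinic-period would give power of about 0.46 to 0.63 for d = 0.20, given the assumed clinic SD and independent ratings; repeated ratings by the same people would alter this. The cross-over analysis of EHR rates is not touched by this point.

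**What to change.** 1. In Quantitative data, take the acceptability, feasibility and appropriateness surveys out of the I-FRESH against standard-care model, and keep that model for the EHR rates.
2. In Power considerations, delete acceptability from the statement of power above 0.83, and keep the statement for the EHR rates.
3. Report mean ratings with 95% confidence intervals at 6 and 12 months, by clinic (half-width about 0.28 SD with 48 parents) and overall with clinic accounted for (0.15 to 0.33 SD for an assumed clinic SD of 0.05 to 0.30; 0.14 SD if clustering is ignored). If a change is wanted, add the 6-to-12-month change and label it as within I-FRESH.
4. In Program acceptability, feasibility, and process evaluation, say that all enrolled parents are surveyed at 6 and 12 months whether or not they engaged with a programme. This is a clarification.

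The cost is wording in three sections. No new data collection is needed.

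### The cross-over effect on acceptability ratings is modelled and powered, but every rating is taken after roll-out, so the effect is not identified

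*Protocol article*

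**What the plan says.** **Outcome status.** Under Specific Aim 2, feasibility and acceptability are named as the primary implementation outcomes.

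**Model.** Quantitative data lists, among the Aim 2 primary analyses, "surveys (e.g., Acceptability, Feasibility, and Appropriateness) across the study period using Generalized Linear Mixed-effects Models (GLMM"), with time-varying indices for clinics crossing over in each wave, a secular time trend and clinic characteristics. The next sentence says that monthly clinic summaries will allow changes after crossing over to be estimated.

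**Power.** Power considerations uses formulas "drawn from stepped wedge designs that account for unequal cluster size and package" swCRTdesign. One sentence sets the inputs, "With alpha = 0.05, 4 clusters (1 clinic per cluster = 4 clinics with" "300 - 500 potential patients in each clinic) and five periods of transitions (baseline and 4 clinics"), and claims that "we will maintain power > 0.83 to detect clinic differences (I-FRESH vs standard care) of >8% in rates of screening", referral and follow-up engagement. The same sentence extends the claim to "changes in acceptability ratings of d > 0.20 after implementing I-FRESH", "given a between clinic standard deviation of 0.05 in random treatment effects".

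**Data collection.** The section on acceptability, feasibility and process evaluation says: "All participants will be invited to complete post-roll-out surveys (every 6 months"), using the three 4-item scales. Parents are surveyed after 6 and 12 months of referral and programme engagement. In Table 1 the first Aim 2 row, which holds these ratings, has frequency 6 and 12 months. The Aim 3 rows of the same table do list month 0. The pre-roll-out activities are qualitative (premortem, periodic reflections) or use a different instrument, the 21-item PRISM Fit survey.

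**The concern.** A stepped-wedge treatment effect compares observations before a clinic crosses over with observations after it, adjusted for calendar time through clinics that have not yet crossed. Both sides must be observed. For the EHR screening rate this can work, because the registry covers all patients attending the participating clinics and can hold standard-care months. For the acceptability scales, no stated administration falls before a clinic's launch.

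Two things are at stake. First, the only power statement for a primary implementation outcome concerns a comparison for which no control data are planned. Second, an analyst who fits the model as described will find the cross-over term inestimable and will have to choose another contrast, such as 12 against 6 months, after seeing the data. An analysis plan written later cannot repair this, because a pre-launch rating that was not taken cannot be recovered once the clinic has started.

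**Working it through.** **1. The plan's own power figure.** Inputs from Power considerations: 4 clusters, 5 periods, alpha 0.05, 300 to 500 patients per clinic, random treatment-effect SD η = 0.05. Assumed, because not given: two-sided test, rating SD σ = 1, between-clinic SD τ from 0.001 to 0.1, and 300 to 500 observations n per clinic-period. Each clinic's vector of period means has covariance

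V = (σ²/n)·I + τ²·J + η²·XX′,

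where J is a matrix of ones and X is the 0/1 treatment vector. Fixed effects are the five periods and the treatment. SE is the square root of the treatment element of (ΣZ′V⁻¹Z)⁻¹, and power = Φ(0.20/SE − 1.96).

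| n per clinic-period | τ | SE | Power for d = 0.20 |
|---|---|---|---|
| 300 | 0.1 | 0.0526 | 0.967 |
| 300 | 0.001 | 0.0468 | 0.990 |
| 500 | 0.1 | 0.0440 | 0.995 |
| 500 | 0.001 | 0.0399 | 0.999 |

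These values are consistent with a claim above 0.83. But X is 0 in 10 of the 20 clinic-periods (4 + 3 + 2 + 1 untreated cells fall in periods 1 to 4), so the calculation assumes ratings in ten standard-care cells. (The exact 0.83 cannot be reproduced, because τ, the baseline rate and n per period are not stated.)

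**2. Which cells the survey schedule fills.** Write L for a clinic's launch month. Ratings fall at L + 6 and L + 12 (for parents, later still, since their clock starts at referral). The cross-over indicator is 1 if t > L. Since L + 6 > L for any L, it is 1 in all 4 × 2 = 8 clinic-by-time cells. None of the ten standard-care cells is filled.

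**3. Rank check.** Columns: intercept, calendar time, three clinic terms, cross-over indicator. Launches at months 3, 7, 11 and 15 are an assumption drawn from the 3-month standard-care period and the 4-month intervals.

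| Ratings taken | Rows | Rank with indicator | Rank without | Estimable |
|---|---|---|---|---|
| 6, 12 months, clinic terms in | 8 | 5 | 5 | no |
| 6, 12 months, clinic terms out | 8 | 2 | 2 | no |
| 6, 12, 18 months, clinic terms in | 12 | 5 | 5 | no |
| pre-launch, 6, 12 months, clinic terms in | 12 | 6 | 5 | yes |
| pre-launch, 6, 12 months, clinic terms out | 12 | 3 | 2 | yes |

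Launches at 6, 10, 14, 18 and at 3, 8, 13, 20 give the same ranks of 5 and 5 for the 6- and 12-month schedule with clinic terms. This must be so: a column of ones equals the intercept under any calendar, and more respondents only repeat the same rows.

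**4. The obvious fallback.** The 12-against-6-month change in paired parent ratings has SE = √(2(1 − r)/N). With N = 192 (240 less 20%) and assumed r = 0.3, SE = √(1.4/192) = 0.085 and power for d = 0.20 is 0.65. With N = 240 and r = 0.7, SE = √(0.6/240) = 0.050 and power is 0.98. It is estimable as a simple change. With clinic terms and linear calendar time in the model it is aliased too (rank 5 with and without), because time since launch equals calendar time minus the clinic's launch month.

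**The case against.** **The words standard care attach only to the rates.** In the power sentence they sit with the rates of screening, referral and follow-up. Acceptability is a second object, worded as a change after implementation, which could mean 6 to 12 months. This is a possible reading of the clause alone. It does not fit the rest of the sentence, which derives the power from a design with a baseline period and a random treatment-effect SD. A 12-against-6-month change is not what those formulas power.

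**The model is not fixed to one 0/1 indicator.** The article speaks of time-varying indices. A time-since-launch index without fixed clinic terms is estimable from post-launch ratings. That stands as algebra, but such an index describes a trend under the programme, not the effect of crossing over.

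**The survey clock might be study time.** If 6 and 12 months were calendar months of the study, clinics not yet launched would supply control ratings and the rank would rise to 6. Table 1 gives no anchor, so the table alone would allow this. The measures text does not: it calls the surveys post-roll-out and times parents from referral and engagement.

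**A pre-launch rating would not be a standard-care rating.** This objection is sound and limits the remedy. Before launch, raters can judge only a programme they have not yet experienced. The PRISM Fit raters are described as representative providers, staff, community stakeholders and administrators, not the full post-roll-out sample, and parents would still have no baseline.

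A reader might also infer that the whole cross-over analysis fails, or that acceptability cannot be assessed at all. The documents support neither. The gap is confined to the survey scales, and the post-roll-out ratings can be summarised and set beside the qualitative data as planned.

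**Conclusion.** The point holds for the acceptability, feasibility and appropriateness surveys. As written, zero of the planned ratings precede roll-out, the cross-over coefficient is not identified at any sample size or launch calendar, and the power above 0.83 for d > 0.20 describes a contrast absent from the data. This is an error in the stated design rather than a detail left to a fuller plan, and it concerns outcomes named as primary for implementation, so it should be corrected.

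The conclusion rests on the stated survey schedule being complete and on post-roll-out meaning after the rater's own clinic has launched. It does not rest on the assumed launch months. It does not extend to the EHR rates or to Aim 3, and it says nothing against the ratings as descriptive evidence.

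**What to change.** **Quantitative data.** Take the three scales out of the cross-over mixed model. Report the 6- and 12-month ratings per clinic and per rater group with 95% confidence intervals, and the trend over successive clinics. With four different clinics, that trend is descriptive.

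**Power considerations.** Delete the acceptability clause from the stepped-wedge sentence, or replace it with the precision of those estimates. For parents in one clinic the half-width in SD units is 1.96/√60 = 0.25 with all 60 responding, and 1.96/√48 = 0.28 after 20% loss.

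**Table 1.** State that 6 and 12 months run from roll-out (for parents, from referral).

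**Optional.** Add the three 4-item scales to the PRISM Fit survey that staff, administrators and community raters complete before each roll-out. Label the result anticipated acceptability and analyse it as a pre/post change in perception, not as I-FRESH against standard care.

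**Cost.** Mainly wording in two paragraphs and one table row. The stated acceptability power disappears or becomes less favourable. The optional step adds twelve short items to an existing survey and must be in place before a clinic launches.
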